(no activity was measured) in the saturated fat diet, but no increase in HDL [26]. However, this study was conducted on a background of a 47% carbohydrate diet and it may be that carbohydrate content modifies the effects of saturated fat. Our previous studies observing increases in HDL and large LDL were performed on a background of a lower carbohydrate intake. Other possible mechanisms that can result in increases in both large HDL and LDL include a reduction in hepatic lipase (HL) activity or an increase in lipoprotein lipase (LPL) activity, and again there is a lack of evidence regarding the effects of saturated fat on these enzyme activities.

We and others have consistently shown that decreases in dietary carbohydrate intake to levels below that of the typical American diet can reduce levels of LDL cholesterol, independent of body weight, even when accompanied by high intakes of saturated fat. This reduction in LDL cholesterol is specifically due to a decrease in small, dense, LDL particles in a manner that is independent of saturated fat intake (**Figure 1** and [3]). We recently demonstrated that a higher (15%) vs. lower (9%) saturated fat content in diets containing 26% carbohydrate and 29% protein increased both HDL cholesterol and total LDL mass and that this was associated with a non-significant increase in large LDL without a change in small LDL. Furthermore, there were no effects of increased saturated fat intake on apoB levels, indicating a change in composition, but not in total number of LDL particles.

**Figure 1.** Left panel: Changes in mass of total LDL and LDL subfractions (large=LDL I, medium=LDL II, and small=LDL III+IV) with reduced carbohydrate intake in 178 overweight and obese men. Right panel: Changes in HDL cholesterol. Changes are in reference to the baseline diet (54% carbohydrate, 16% protein, 30% fat, 7% saturated, 13% monounsaturated). After

one week on the baseline diet subjects were randomized to 4 weeks of the baseline diet, or diets with reduced content of carbohydrate (39% or 26% together with increased protein (29%)). For the lowest carbohydrate intake (26%), there was also an increase in fat intake (45%), achieved either with low saturated fat (9% saturated, 27% monounsaturated or high saturated fat (15% saturated, 20% monounsaturated). Body weight was constant.

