## Data Analysis

The hypothesis that increased saturated fat derived primarily from dairy products will increase levels of large HDL2 and large LDL in pattern B individuals, with no significant effect on small, dense LDL, will be tested by comparing the mean change in large LDL levels as measured by ion mobility. The statistical significance will be evaluated by one-way analysis of variance with the factor being high or low saturated fat intake. Similar analyses will be used to test the effects of saturated fat on HDL cholesterol, and LDL diameter. Comparison of LDL pattern conversion rate between high and low saturated fat diets will be analyzed by Chi-squared analysis.

**Table 1** shows the detectable and expected differences using data from the high fat/low fat study described above [27]. Expected differences are derived from correlations of the change in fatty acid intake (assessed by food records of prescribed diets) and change in LDL measurements. The correlations were used to select the differences in SFA (12%), myristic (2.5%), and palmitic acid (5.5%) levels needed for a detectable effect in the primary endpoints given 25 subjects per group. These are approximately equal to the mean change in intake in our previous study. With 25 subjects/group, we have adequate power (80%) to detect the expected changes in LDL I, LDL diameter, and HDL2b given either a 12% difference in saturated fat or a 2.5% difference in myristic acid between the two diets. Although the lipoprotein subfraction predictions are based on measurements made by analytical ultracentrifugation or gradient gel electrophoresis, we expect the ion mobility method to be equally or more

precise. Typical standard deviations for measurements by ion mobility are 20.9 mg/dl for large LDL and 3.5 Å for LDL diameter. In addition, we will use the average value of measurements from two blood draws on consecutive days to reduce variance and increase power.

**Table 1:** Detectable (80% power) and expected difference for primary endpoints

|               | SD of difference | Detectable differences between groups  |            | Expected Difference w/ 12% ΔSFA | Expected Difference w/ 2.5% Δ14:0 |
|---------------|------------------|----------------------------------------------------|------------|---------------------------------|-----------------------------------|

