|               |                  | Difference                                         | % baseline |                                 |                                   |
| HDL2b (mg/dl) | 11.5             | 6.5                                                | 25         | 7.9 mg/dl                       | 10.7 mg/dl                        |
| LDL-I (mg/dl) | 29.6             | 16.6                                               | 22         | 39.2 mg/dl                      | 49.6 mg/dl                        |
| LDL diam (Å)  | 5.0              | 2.9                                                | 1.7        | 4.9 Å                           | 6.1 Å                             |

Detectable differences assume the average of 2 baseline and 2 post-diet measurements

To estimate predicted LDL pattern conversion rates, we used logistic regression to achieve a best approximation of the expected conversion rate between the two diets. At 35% carbohydrate intake and 12% difference in saturated fat, we expect that 48% pattern B participants will convert to pattern A. With a 2.5% difference in myristic acid, we predict a 71% conversion rate. Similar power estimates were obtained with a 5.5% difference in palmitic acid.

Other endpoints will include plasma triglyceride, total cholesterol, LDL-cholesterol, HDL cholesterol, apoB, apoAI, and LDLII-IV. **Table 2** presents the detectable differences in these endpoints estimated at 80% statistical power, 5% significance using baseline concentrations and standard deviation of response observed in our previous controlled dietary trials. Detectable differences are in accordance with power estimates from previous diet studies.

Sample size estimation is determined by lipoprotein endpoints, as not enough data is available to estimate expected differences in CETP, HL, and LPL activity levels. Based on previous data, we have adequate power (86%) to detect a difference of 15% baseline levels of HL activity between groups and reasonable power (52%) to detect a difference of 30% baseline levels of LPL between groups.

**Table 2.** Detectable differences (80% power) in other plasma lipid and lipoprotein levels

|                            | Baseline concentrations | Standard deviation of difference | Differences between groups         |            |
|----------------------------|-------------------------|----------------------------------|------------------------------------|------------|

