|                            |                         |                                  | Detectable Difference  | % baseline |
| Triglycerides (mg/dL)      | 215.31±106.34           | 117.97                           | 65.98                              | 30.65      |
| Total cholesterol (mg/dL)  | 206.79±32.53            | 25.97                            | 14.52                              | 7.02       |
| LDL-chol(mg/dL)            | 127.55±30.19            | 24.60                            | 13.76                              | 10.79      |
| HDL-C(mg/dl)               | 36.49±6.05              | 5.34                             | 3.05                               | 8.36       |
| Apo AI (mg/dL)             | 109.21±14.17            | 9.49                             | 5.31                               | 4.87       |
| Apo B (mg/dL)              | 99.78±18.03             | 25.50                            | 14.26                              | 14.29      |
| LDL-2 (mg/dL)  | 90.03±38.62             | 35.00                            | 19.58                              | 21.75      |
| LDL-3 (mg/dL)  | 91.33±28.76             | 25.02                            | 13.99                              | 15.31      |
| LDL-4 (mg/dL)  | 18.72±14.39             | 15.71                            | 8.78                               | 46.92      |

Detectable differences assume the average of 2 baseline and 2 post-diet measurements

LDL subfraction data for this table was derived from a more recent study than data shown in Table 1, but show very similar % baseline differences.

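### In Table 2 the apo B SD of difference (25.50) is exactly √2 times the baseline SD (18.03), so one cell was very probably derived from the other and both need checking against source

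*Protocol*

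**What the plan says.** All in the Protocol:

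- **Data Analysis, text before Table 2.** The detectable differences for the other endpoints, apo B among them, are "estimated at 80% statistical power, 5% significance", "using baseline concentrations and standard deviation of response observed in our previous controlled dietary trials". The group size, given earlier in the section, is 25: "With 25 subjects/group, we have adequate power (80%).
- **Table 2, apo B row.** "Apo B (mg/dL) | 99.78±18.03 | 25.50 | 14.26 | 14.29": baseline mean and SD, SD of difference, detectable difference, and that difference as a percentage of baseline.
- **Table 2, comparison rows.** "LDL-chol(mg/dL) | 127.55±30.19 | 24.60 | 13.76 | 10.79" and "Apo AI (mg/dL) | 109.21±14.17 | 9.49 | 5.31 | 4.87".
- **Table 2, footnote 1.** "Detectable differences assume the average of 2 baseline and 2 post-diet measurements".
- **Clinical Procedures, plasma analyses.** Apolipoproteins are listed for V2a and V3a. The lists for V2b and V3b contain lipids and ion mobility subfractions but no apo B.
- **Background.** Of an earlier study: "there were no effects of increased saturated fat intake on apoB levels, indicating a change in composition, but not in total number of LDL particles".

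No post-diet SD, within-person correlation or derivation is given for apo B.

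**The concern.** An SD of change measured in the same people normally reflects the correlation between their two readings, and with positive correlation and similar SDs it falls below √2 times the single-reading SD. The apo B figure sits exactly at √2 times, which is what results when someone has only a baseline SD and treats the two readings as independent. That is hard to reconcile with a column described as observed responses.

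The stake is modest but real. The Background uses unchanged apo B as evidence that saturated fat alters LDL composition and not particle number. Anyone reading a null apo B result that way will ask how large a rise the trial could have missed, and Table 2 is where the protocol answers.

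**Working it through.** **Inputs.** Table 2 (means, baseline SDs, SDs of difference, detectable differences); 25 per group, 80% power and 5% significance from Data Analysis, taken as two-sided; two-draw averaging from footnote 1.

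**1. Reproduce the stated figure.** Normal approximation, with averaging taken to divide the SD by √2:

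(1.960 + 0.842) × √(2/25) × 25.50/√2 = 0.5603 × 25.50 = 14.29 mg/dL, against 14.26 stated.

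The table's own multiplier is 14.26/25.50 = 0.5592, the same as the other rows to within rounding (0.559 to 0.560) except HDL-C (0.571). Also 14.26/99.78 = 14.29%. The row follows correctly from 25.50; the question is where 25.50 came from.

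**2. Test the identity.** 18.03 × √2 = 25.498, which rounds to 25.50.

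**3. Implied correlation in each row.** With equal SDs before and after diet, SD_diff² = 2 × SD_base² × (1 − r), so r = 1 − SD_diff²/(2 × SD_base²).

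| Row | SD_base | SD_diff | Ratio | Implied r |
|---|---|---|---|---|
| Triglycerides | 106.34 | 117.97 | 1.109 | 0.38 |
| Total cholesterol | 32.53 | 25.97 | 0.798 | 0.68 |
| LDL-C | 30.19 | 24.60 | 0.815 | 0.67 |
| HDL-C | 6.05 | 5.34 | 0.883 | 0.61 |
| Apo AI | 14.17 | 9.49 | 0.670 | 0.78 |
| **Apo B** | **18.03** | **25.50** | **1.414** | **0.00** |
| LDL-2 | 38.62 | 35.00 | 0.906 | 0.59 |
| LDL-3 | 28.76 | 25.02 | 0.870 | 0.62 |
| LDL-4 | 14.39 | 15.71 | 1.092 | 0.40 |

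Only apo B shows the √2 relation.

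**4. Which cell is more suspect?**

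- Baseline SD as a share of the mean: apo B 18.03/99.78 = 18.1%, between total cholesterol (15.7%) and LDL-C (23.7%). This is unremarkable.
- SD of difference as a share of the mean: apo B 25.50/99.78 = 25.6%, against LDL-C 19.3%, total cholesterol 12.6% and apo AI 8.7%. This is high for a measure of this kind.
- If 25.50 were right and apo B had the other rows' ratios, the baseline SD would be 25.50/1.109 = 23.0 up to 25.50/0.670 = 38.1, that is 23% to 38% of the mean.

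These comparisons point to 25.50 as the derived cell, without proving it.

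**5. Size if 25.50 is the derived cell.** The documents give no apo B correlation, so the range of the other rows is borrowed as an assumption. SD_diff = 18.03 × √(2(1 − r)). The two-draw column uses the table's multiplier, 0.5592. The one-draw column uses 0.8087 (two-sample t, 25 per group).

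| Assumed r | SD of change | Two draws per phase | One draw per phase |
|---|---|---|---|
| 0.38 (triglycerides) | 20.0 | 11.2 | 16.2 |
| 0.67 (LDL-C) | 14.7 | 8.2 | 11.9 |
| 0.78 (apo AI) | 12.1 | 6.8 | 9.8 |

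Detectable differences are in mg/dL.

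**6. Size if 25.50 is correct.** On the two-draw convention 14.26 stands. With one draw per phase the detectable difference is 0.8087 × 25.50 = 20.6 mg/dL.

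**The case against.** The strongest reply is that no arithmetic error has been shown. The row is internally consistent, and the doubt concerns an input whose source is not visible. Three parts of that reply stand.

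- **The relation runs both ways.** 25.50/√2 = 18.03 is also the working SD once the two-draw averaging is applied. If that number was copied into the baseline cell, 25.50 was observed, 14.26 stands on the table's convention, and ±18.03 is the error. The text's ion mobility SDs show the same link to Table 1 (20.9 × √2 = 29.6; 3.5 × √2 = 4.95, tabled as 5.0). So √2 conversions appear to have been in use, but their direction cannot be told.
- **Zero correlation depends on equal SDs.** With post-diet SDs of 22 or 24, r = (18.03² + SD_post² − 25.50²)/(2 × 18.03 × SD_post) would be 0.20 or 0.29. A reader might infer that 25.50 is proven not to be an observed SD; the protocol does not show that.
- **Direction is open.** A reader might infer that 14.26 is too pessimistic. That holds on the two-draw convention, where 11.2 to 6.8 lies wholly below it. With apo B scheduled once per phase, the range of 16.2 to 9.8 contains 14.26, and if 25.50 is right the one-draw figure is well above it.

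The reply also rightly limits the importance. Apo B is listed among the other endpoints, none of the three stated hypotheses names it, and ion mobility is described as counting particles directly.

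What the reply does not remove is the coincidence. Agreement to four figures, in the one row out of nine that implies no within-person correlation, is very unlikely if both cells are separately observed statistics.

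**Conclusion.** The point holds as a discrepancy between the apo B row and its stated source. One of the two SDs was very probably derived from the other, and 25.50 is the likelier. If so, the 80%-power figure of 14.26 mg/dL does not rest on an observed SD of response.

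The numerical consequence is conditional: about 11.2 to 6.8 mg/dL with two draws per phase, or 16.2 to 9.8 mg/dL with one. Both ranges assume that 18.03 is right, that SDs are equal before and after diet, and that apo B shares the correlations implied by the other rows. The net direction of any error in 14.26 is not established. The sample size of 50 is set by the lipoprotein endpoints and does not change.

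**What to change.** 1. Check both apo B cells, 18.03 and 25.50, against the source trials and correct whichever was derived.
2. Recompute the detectable difference and its percentage of baseline from the observed SD of within-person apo B change, using the number of apo B draws scheduled under Clinical Procedures (V2a and V3a only). If a second apo B draw is intended, add it to the V2b and V3b lists so that footnote 1 applies.
3. If no observed SD of change exists, say that the figure assumes zero within-person correlation, except the apo B row from the statement that the SDs were observed, and give the range above with its assumption.

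The cost is one table row and a sentence. Sample size is untouched, and so are the visits unless a second apo B assay is added on blood already drawn.
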